#### Statistical analyses for primary outcome measures

##### Clinical outcomes

Statistical analysis of the data will follow intention-to-treat principles [101], i.e. “1) keep participants in the intervention group to which they were randomized, regardless of the intervention they actually received; 2) measure outcome data on all participants; 3) include all randomized participants in the analysis.” Baseline sociodemographic and clinical status (type of anxiety disorder, comorbidity, symptom severity, functional status, current treatment) will be described by intervention group. A mixed effects regression model will be used to account for between- and within-subject variations in the longitudinal effects of the intervention on the primary outcome measures of anxiety. Such model will allow for the inclusion of patients with missing data at any of the follow-up interviews as well as the within effect of intervention (maintenance of gains within individuals). The effects of treatment will also be adjusted for three covariates: a) comorbid depressive symptoms (continuous; PHQ-9 score); b) psychotropic medication (yes or no); c) specific anxiety disorder (ADIS-5). This set of variables will be added to the mixed regression model described above to better understand the additive contribution of each variable to the relationship between the study groups and anxiety. Functioning and quality of life outcomes also measured longitudinally will be analyzed in a similar fashion (a generalized estimating equation (GEE) with a logit-link function regression model will be used when necessary). Sub-group analyses for the presence of an antidepressant and/or benzodiazepines medication, the principal anxiety disorder at baseline and gender are planned. Treatment effect sizes will be calculated with Cohen’s d for each sub-group of interest. Compliance rates (number of sessions completed) will be compared using t-tests. Additionally, sensitivity analysis [102] will be conducted to assess the impact of missing data on estimates of treatment effects with an adequate multiple imputation statistical technique [102] and without imputation (i.e. available case analyses), as well as for outlying observations and “per protocol”. Reporting of sensitivity analysis will provide valuable information on the robustness of results.

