## Methods

### Participants, interventions and outcomes

#### Study setting

The trial is being conducted in three health and social service administrative regions in the province of Québec, Canada. The network organization in Québec comprises regional integrated health and social services centres accountable for the delivery of care and services within a population responsibility framework. The universal health insurance system provides health care and social services coverage for the population. However, the organisation and delivery of mental health care varies considerably within each administrative region, and the same variability also applies to complementary mental health services available in the private sector (e.g., psychologists in private practice). We purposefully selected the following three study sites based on diversity (e.g., population size, region, university teaching hospital, psychiatric hospital, primary care mental health services, primary care network). The integrated health and social services centre for Quebec City and adjacent areas (i.e. *CIUSSS de la Capitale-Nationale)* serves an urban and rural population of 737,000 inhabitants over a large territory of 18,600 KM^2^; the study site is in the Quebec City region (89% of the territory population). The health and social services centre for the region of Laval (i.e. *CISSS de Laval*) serves a predominantly urban population of 435,000 inhabitants and is part of the Greater Montreal metropolitan area (over four million inhabitants). The health and social services centre for the Estrie region (i.e. *CIUSSS de l’Estrie - Centre Hospitalier universitaire de Sherbrooke)* serves a population of 474,000 inhabitants over a large territory of 13,000 km^2^; the study site is in Sherbrooke (> 164,000 inhabitants). All selected sites agreed to provide in-kind support for the study, including: 1- public sector psychologists and psychotherapists participation as co-therapists in treatment groups; 2- office space in primary care settings for participant’s assessment and treatment delivery. The institutional review boards at each site approved the protocol.

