### Assignment of interventions: Sequence generation, allocation concealment mechanism and implementation

Randomization is at the patient level. Contamination is unlikely because specific CBT treatments for anxiety disorders are rarely available in primary care in our health care context. To ensure that comparable groups are obtained, stratification based on site is implemented. To ensure a balance in the allocation for the strata and thus eliminate the risk of a secular trend in the composition of groups, blocks of four are used. This strategy also helps to avoid differences in the composition of the two groups, in the event of changes in clinical characteristics of those involved in the study over time. Randomization is being carried out using a code generated by a statistical software (manages the stratification and blocks) with a ratio of 1:1, set up by an independent statistician who is not be involved in the recruitment.

Allocation concealment is ensured by an online computer tool for clinical trials (PIERCE) that only releases the randomization code to the principal investigator (PR) after the baseline assessment is completed. Upon review of data entry on the PIERCE computer tool from research coordinator and clinical evaluators concerning inclusion and exclusion criteria, written informed consent, agreement to accept the randomly assigned treatment and returned participant’s questionnaire booklet, a computer command allows release of the randomization code (PR). Each member of the team (research coordinator, clinical evaluators, principal investigator) has his or her own access code to the PIERCE system, designed with several access layers, and the randomization module is only accessible to the principal investigator (PR). She informs the research coordinator of each treatment assignment based on the allocation sequence, and the treatment allocation is be communicated to participants by telephone within 2 weeks after the initial clinical interview and reception of the booklet.

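### The listed covariates leave out site, the only stratification factor, and the role of the pre-randomisation outcome in the mixed model is not fixed; settling both would gain precision at almost no cost

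*Protocol article*

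**What the plan says.** All references are to the protocol article.

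- **Randomisation** (Assignment of interventions). "To ensure that comparable groups are obtained, stratification based on site is implemented", and within sites "blocks of four are used". No other stratification factor is named.
- **Primary model** (Clinical outcomes). "A mixed effects regression model will be used to account for between- and within-subject variations in the longitudinal effects of the intervention on the primary" anxiety outcomes. The model is also meant to give "as well as the within effect of intervention (maintenance of gains within individuals"). Its fixed effects are not written out.
- **Covariates** (same section). "The effects of treatment will also be adjusted for three covariates: a) comorbid depressive symptoms (continuous; PHQ-9 score"), then psychotropic medication as yes/no and the specific anxiety disorder from the ADIS-5. These three are added to the mixed model already described. Neither site nor baseline BAI or CSR is among them, and site is not mentioned elsewhere in the analysis text as a fixed or random effect.
- **Baseline data** (Table 2; Participant timeline). The ADIS-5 interview and the booklet containing the BAI are both completed before randomisation.
- **Sample size.** A univariate comparison at post-treatment, d = 0.45, two-sided alpha 0.03, 80% power: 182 patients, raised to 215 for 15% loss.

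**The concern.** Stratifying by site balances site between the arms, so most of the between-site variance is removed from the true sampling variance of the treatment estimate. A post-treatment model without site still counts that variance as error. Its standard error is then larger than the design warrants, and the test is conservative.

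The two primary outcomes at baseline are likely to be strong predictors of their own values at T1. How much of that information is used depends on how T0 enters the model:

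- **T0 not used:** the information is lost.
- **T0 as a repeated response with free arm means:** the T1 group-by-time contrast is a comparison of change scores, which is less efficient than baseline adjustment.
- **T0 as a response with arm means constrained equal, or as a covariate:** the gain is obtained.

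The text is compatible with all three. What is at stake is power and the calibration of standard errors. Validity is not at issue.

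**Working it through.** **1. Reproduce the plan's figure.** Inputs from Sample size: d = 0.45, two-sided alpha 0.03, power 0.80.
- Normal approximation: n per arm = 2(z₀.₉₈₅ + z₀.₈₀)²/d² = 2(2.170 + 0.842)²/0.45² = 89.6, so 90 per arm and 180 in total.
- Noncentral t: 90.8, so 91 per arm and 182 in total, as stated.
- Loss: 182/0.85 = 214.1, so 215, as stated.

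The plan's size therefore relies on neither site nor baseline adjustment.

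**2. Site, for a post-treatment comparison.** Let s be the share of outcome variance between sites. The documents do not give it; I assume 2-5%. The true variance is proportional to 1 − s, while a model without site estimates about 1.
- SE overstatement = 1/√(1 − s): 1.010 at 2%, 1.026 at 5%.
- True alpha = 2[1 − Φ(2.170/√(1 − s))]: critical values 2.192 and 2.226, giving 0.0284 and 0.0260 in place of 0.03.
- Power with site in the model (noncentral t, 91 per arm): 80.9% at 2% and 82.2% at 5%, against 80.1% with s = 0.

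**3. Site, for a change contrast.** A stable additive site effect is the same at T0 and T1 and cancels from each patient's change. A simulation under the null (three sites, blocks of four, within-site T0-T1 correlation 0.5, 40,000 runs) gave these rejection rates at nominal 0.03:

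| Site share | Change contrast | Post-treatment only |
|---|---|---|
| 2% | 0.031 | 0.028 |
| 5% | 0.029 | 0.027 |

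The change contrast is at nominal within simulation error. The site harm in step 2 and the change-score harm in step 4 therefore belong to different models and must not be added together.

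**4. Baseline.** Let r be the T0-T1 correlation, with equal variances at the two times. The documents do not give r. The 0.7 in Sample size is the correlation between the two primary outcomes and cannot stand in for it. Relative to a post-only comparison, the variance is 2(1 − r) for a change contrast and 1 − r² with baseline adjustment or equal constrained baseline means; their ratio is (1 + r)/2 in favour of adjustment. Normal-approximation power = Φ(3.035/√V − 2.170), where 3.035 = 0.45/√(2/91).

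| Assumed r | V change | V adjusted | Ratio | Power, change | Power, adjusted |
|---|---|---|---|---|---|
| 0.4 | 1.20 | 0.84 | 0.70 | 73% | 87% |
| 0.5 | 1.00 | 0.75 | 0.75 | 81% | 91% |
| 0.6 | 0.80 | 0.64 | 0.80 | 89% | 95% |

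Post-only power on the same approximation is 81%. Noncentral t gives values lower by less than one percentage point. Over a wider range, noncentral t gives 64.7% (change) against 83.9% (adjusted) at r = 0.3, and 95.8% against 98.0% at r = 0.7.

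**The case against.** **The baseline part depends on a reading that the text does not settle.** A longitudinal model for within-person effects may well hold T0 as a response. If the arm means at T0 are constrained equal, the gain in step 4 is already obtained. A condensed article may also leave such parameterisation to a fuller document. This stands against any claim that the model omits the baseline outcome, which a reader might infer from the covariate list. The documents show only that its role is not stated.

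**The three covariates may be a second, explanatory step.** They are added to a base model in order to understand what each contributes, so they do not strictly define the primary model. That is a fair reading. Even so, the list is counted and itemised, and it leaves out the one factor that the design stratified on; nothing in the description of the base model supplies site.

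**The site harm is small and conservative.** This stands in full, and for a change contrast it largely disappears. A site-by-time effect would not cancel, but the documents give no figure for one.

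**The support for site differences is loose.** Study setting says that "the organisation and delivery of mental health care varies considerably within each administrative region". That describes variation within regions and is not evidence that outcomes differ between sites. The purposeful choice of three diverse sites is better support, though it too gives no figure.

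**No planned power is lost.** Correct: 182 and 215 reproduce without either adjustment. Among the three main scenarios, only a free-baseline change contrast at r = 0.4 falls below 80%.

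**Conclusion.** The point holds as a low-cost improvement in precision. Site, the sole stratum, is absent from the named covariates, and the use of the pre-randomisation BAI and CSR is not fixed.

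The site effect is modest: standard errors 1-3% too large and true alpha 0.026-0.028, for a post-treatment comparison with an assumed 2-5% site share. The baseline effect could be larger, 14, 10 and 6 percentage points of power at assumed r of 0.4, 0.5 and 0.6, but only if T0 enters with free arm means. It is zero if those means are already constrained equal. Adjusting for PHQ-9 and the other two covariates may narrow the gap.

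A reader might infer that the treatment estimate is biased, that type I error is inflated, or that the trial is underpowered. The documents support none of these: allocation is randomised, leaving site out makes the test conservative, and the sample size was set for an unadjusted comparison.

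**What to change.** - Add site as a fixed effect in the primary and secondary models.
- State in one sentence how T0 enters. Either treat it as a response with means constrained equal between arms and time categorical, or enter baseline BAI (or CSR) as a covariate interacting with time. The constrained form keeps every randomised patient in the model, which fits the article's intention-to-treat rule.
- Settle the wording before the A/B treatment codes are broken, so that the choice cannot follow the results.

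The cost is analysis wording and 2 degrees of freedom for three sites. No new data are needed and the sample size does not change.

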#### Secondary questions

a) Considering clinically significant outcomes for patients with anxiety disorders, is there a significant difference between groups in terms of remission rates and high-end functioning rates based on a clinician-rated measure? b) Is there a significant difference between groups on functioning and quality of life? c) Is there a differential treatment effect size based on diagnostic-specific measures for subgroups of patients meeting DSM-5 criteria for specific anxiety disorders at baseline? d) Is there maintenance of gains at follow up? e) Does the severity of depressive symptoms at baseline moderate treatment effectiveness for the primary outcome measures? f) Does the presence of an antidepressant and/or benzodiazepine medication at baseline moderate treatment effectiveness for the primary outcome measures? g) Is there differential treatment effectiveness based on the principal anxiety disorder at baseline? h) Is there a differential compliance rate and treatment effect size based on gender? i) Is tCBT as a complement to TAU preferable to TAU only based on a cost-effectiveness and cost-utility analysis (i.e., economic evaluation, not described in the protocol)? j) What are the acceptability and feasibility of the tCBT intervention for patients and therapists (i.e., embedded qualitative study, not described in the protocol)?

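### The question whether baseline depression moderates the treatment effect has only an additive covariate to answer it; for medication, principal disorder and gender no between-subgroup comparison is stated

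*Protocol article*

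**What the plan says.** The protocol article, under Secondary questions, asks four things about effect modification:

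- Question e concerns depression and is worded as follows: "Does the severity of depressive symptoms at baseline moderate treatment effectiveness for the primary outcome measures"
- Question f puts the same query for patients who take an antidepressant or a benzodiazepine at entry.
- Question g asks whether patients with different principal disorders respond differently.
- Question h concerns men and women and has two halves, one on attendance and one on effect: "Is there a differential compliance rate and treatment effect size based on gender"

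The section Clinical outcomes, under the statistical analyses, offers two tools that bear on these questions.

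- **Covariates.** "The effects of treatment will also be adjusted for three covariates", namely PHQ-9 score (continuous), psychotropic medication (yes/no) and specific anxiety disorder. Their purpose is given as: "This set of variables will be added to the mixed regression model described above to better understand the additive contribution of each variable".
- **Subgroups.** Three factors are listed: medication, principal disorder and gender. The stated output is: "Treatment effect sizes will be calculated with Cohen’s d for each sub-group of interest".

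Numbers of sessions completed are to be compared by t-tests. No treatment-by-covariate term and no comparison between subgroups is mentioned, and depression is not in the subgroup list.

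**The concern.** A moderation question asks whether the treatment effect varies with a patient characteristic. Adjusting for that characteristic answers something else: what the common treatment effect is once the characteristic is held fixed. If the text is followed as written, question e ends with an adjusted treatment effect and a PHQ-9 coefficient, and neither says whether more depressed patients gain more or less.

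For f, g and the effect-size half of h the gap is smaller. Effects by subgroup will be estimated, but a list of d values without an estimate of their difference and its uncertainty leaves the reader to judge a difference that may be noise. The Discussion intends the results to guide decision makers, managers and clinicians, and it names comorbid depression and concomitant medication as features of the sample. Statements about who benefits are therefore likely to be used.

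**Working it through.** **1. Question set against method**

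| Question | Adjustment covariate | Planned subgroup | Between-level comparison stated |
|---|---|---|---|
| e, baseline depression | yes (PHQ-9) | no | none |
| f, medication | yes (any psychotropic) | yes (antidepressant and/or benzodiazepine) | none |
| g, principal disorder | yes | yes | none |
| h, gender: effect size | no | yes | none |
| h, gender: compliance | not applicable | not applicable | t-test |

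**2. Why the additive term cannot answer e**

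Write the model at a given visit as Y = b0 + b1·T + b2·X, with T the treatment and X the baseline PHQ-9. The treatment effect at any X is b1, whatever the data. With Y = b0 + b1·T + b2·X + b3·T·X it becomes b1 + b3·X, and b3 is the moderation. Letting b1 differ by visit, as a longitudinal model does, still leaves it free of X.

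**3. The plan's own sample size**

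Inputs from Sample size: d = 0.45 at T1, two-sided alpha 0.03, power 80%, 15% loss.

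- Two-sample t-test with the noncentral t distribution: 91 per arm, 182 in total, power 0.801. This reproduces the stated 182.
- 182 / 0.85 = 214.1, rounded up to 215. This also reproduces.

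Both figures concern the overall comparison of the arms. The article gives none for moderation.

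**4. How noisy a difference between two subgroup d values is**

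Assumptions, not in the article: a binary moderator whose smaller group has share p = 0.5, 0.3 or 0.2; equal allocation within each subgroup; SD 1; one T1 measure without baseline adjustment; normal approximation.

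SE(d1 − d2) = √[4/(N·p) + 4/(N·(1 − p))] = √[4/(N·p·(1 − p))], with N = 182:

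- p = 0.5: √(4/45.5) = 0.296
- p = 0.3: √(4/38.22) = 0.324
- p = 0.2: √(4/29.12) = 0.371

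Chance of an observed difference above 0.3 with no true moderation, 2·[1 − Φ(0.3/SE)]: 31%, 35% and 42%.

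Power of the interaction test for a true difference of 0.45, as large as the planned overall effect, Φ(0.45/SE − z) plus a negligible opposite tail:

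| p | alpha 0.05 (z = 1.96) | alpha 0.03 (z = 2.17) |
|---|---|---|
| 0.5 | 33% | 26% |
| 0.3 | 29% | 22% |
| 0.2 | 23% | 17% |

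A repeated-measures model with baseline adjustment would do somewhat better. The figures do not apply directly to e, where PHQ-9 is continuous, or to g, where Eligibility criteria lists four disorders.

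**The case against.** The strongest reply has three parts.

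**The wording is loose.** The covariate sentence goes on to name the relation between study group and anxiety as its target, so the authors may have had effect modification in mind. That is possible, but covariates described as adjustment, with an additive contribution, do not amount to an interaction. Depression has no second route through the subgroup list.

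**For f, g and h, the article is condensed and an analysis plan may exist.** The subgroup factors match these questions one for one, and nothing excludes an interaction test. This stands. For these three one can say only that the named output does not compare subgroups, not that no comparison will be made. The compliance half of h has its own t-test and falls outside the point.

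**The consequence depends on how results are read.** A reader might infer that subgroups will be judged by which one reaches significance, so that false moderation claims follow in about half of trials or more. The article states no subgroup significance test, so that error rate does not belong to its plan. A reader might also infer that an interaction test would bring the 31-42% of chance differences down to 5%. It would not: observed d values scatter just as much either way. The test only holds the rate of false claims of moderation at its nominal level.

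**Conclusion.** The point holds fully for question e: a stated question is paired with a stated method that cannot answer it, and no other analysis of it is given. It holds in weaker form for f, g and the effect-size half of h, where separate d values are the only named output.

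A reader might conclude that all four questions lack a usable analysis. The documents do not support that, because subgroup analyses are planned for three of them.

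The size (SE of about 0.30-0.37 for a difference in d, chance differences above 0.3 in about 31-42% of trials, interaction power of 17-33% for a difference of 0.45 across the two alpha levels) is illustrative and rests on the assumed binary splits and the single unadjusted T1 measure. These are secondary questions; the primary comparison and its sample size are untouched. The change should be made, but the trial's main result does not depend on it.

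**What to change.** - **Question e:** add a treatment × baseline PHQ-9 term, with PHQ-9 continuous, to the mixed model for each primary outcome.
- **Questions f, g and the effect-size half of h:** add treatment × medication, treatment × principal disorder and treatment × gender terms. Define medication as question f does, since the covariate is the broader psychotropic category. Principal disorder, with four categories, needs up to three interaction terms.
- **Reporting:** give each interaction estimate at T1 with its confidence interval as the answer to the question, crossing the terms with visit as far as that requires. Keep the subgroup d values as description only.
- **Status:** label these analyses exploratory. Given the low power, a non-significant interaction should not be reported as absence of moderation.

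The cost is a few lines of analysis text. All the variables are already in the planned assessments or analyses, so no data, visits or patients are added. By the Trial status section, enrolment had closed while the last treatment group was still to finish, so the wording could be settled before the outcome data were complete.
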